### Data management {19}

Database set-up, double-entry data collection, data storage, and data validation are the responsibility of the principal investigator’s study centre. All data management processes will be performed according to standard operating procedures (SOPs). Data validation includes checking the completeness, consistency and plausibility of the data documented in the CRF. For this purpose, a query system will be set up between data management and the investigator. In the so-called query process, requests for clarification of incomplete, implausible, and/or inconsistent data will be made as quickly as possible to the investigator by the data management team. These queries will be answered by the investigator or a person appointed by the investigator and transmitted to the data management team for entry into the database. After all queries for all included patients have been clarified, the database will be closed at the end of the study and handed over to the biometrician for evaluation. After completion of all evaluations and preparation of the final report, the originals of all CRFs will be transferred to the PI for archiving. After completion of the study, the data will be converted into different data formats (e.g. csv files) to ensure further use. The primary data on which the scientific publications are based will be publicly accessible for reanalyses and meta-analyses in the BioStudies public repository [15] after completion of the study.

### Confidentiality {27}

During the study, medical findings and personal information of the patient will be collected and stored in writing or electronically at the study site. The data important for the study will be additionally stored and evaluated in pseudonymised form. Pseudonymized means that no names or initials are used, but only a numerical and/or letter code, possibly with an indication of the year of birth. The data will be secured against unauthorized access. The patient has the right to information about the data stored about him or her (Art. 15 DS-GVO). If it is established that incorrect personal data regarding a patient are being processed, he or she may request that it be corrected (Art. 16 DS-GVO). He or she also has the right to request the deletion of his or her personal data if certain reasons for deletion exist. This is the case, for example, if the personal data are no longer necessary for the purpose for which they were originally collected or processed or if he or she withdraws his or her consent and there is no other legal basis for the processing (Art. 17 DS-GVO). The patient also has the right to restrict the processing of his or her personal data (Art. 18 DS-GVO), a right to data portability (Art. 20 DS-GVO), and a general right of objection (Art. 21 DS-GVO). For enquiries and complaints in this regard, the patient will be given the relevant contact addresses along with the other study information. This includes the contact data of the hospital, the investigators, the data protection officer, and the State Commissioner for Data Protection of the study centre.

### Plans for collection, laboratory evaluation, and storage of biological specimens for genetic or molecular analysis in this trial/future use {33}

N/A, as no biological samples will be collected from the study participants.

## Statistical methods

### Statistical methods for primary and secondary outcomes {20a} and for additional analyses (e.g. subgroup analyses) {20b}

An intention-to-treat analysis will be performed. Continuous variables will be reported as medians with their ranges (minimum and maximum), while categorical variables will be reported as frequencies and percentages, unless otherwise stated. For continuous variables, differences between treatment arms will be analysed using linear regression, potentially correcting for confounders such as study centre, age, anticoagulation and/or antiplatelet drugs, Forrest classification, ulcer size and location, *Helicobacter pylori* positivity, prior endoscopic treatment, and standard or bipolar haemostatic forceps therapy; categorical and binary outcomes will be analysed using logistic regression, also potentially correcting for the above confounders. Bonferroni correction will be applied to subanalyses of statistically significant tests. Corrected *p* values < 0.05 will be considered significant. Variables with a *p* value < 0.05 in the univariate model will be entered into a multivariate stepwise logistic regression model (forwards selection, likelihood ratio) to assess the independent predictive effect of the variables of interest. Statistical analysis will be performed using SPSS (version 24.0; IBM, New York, NY), Stata software (V.15; StataCorp, College Station, TX), or R (version 3.3.0 or newer).

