
### Objectives {7}

The efficacy and safety of bipolar haemostatic forceps should be investigated in the primary treatment of active, nonvariceal upper gastrointestinal haemorrhage of any cause (except tumour haemorrhage) in a randomized, prospective, multicentre superiority trial. In this setting, bipolar haemostatic forceps are the experimental study arm, and the standard therapy of haemoclip + / − epinephrine injection is the comparator study arm. The primary objective is the combined endpoint of successful initial endoscopic haemostasis and the absence of rebleeding within 30 days after successful initial haemostasis. Secondary objectives are the number of salvage procedures such as OTSC, angiography + coiling or surgery for primary haemostasis, type and number of therapy-associated complications, number of endoscopic reinterventions in 30-day intervals, number of blood units transfused, length of hospital stay, length of intensive care unit stay, and 30-day mortality.

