### Criteria for discontinuing or modifying allocated interventions {11b}

If no haemostasis is achieved, it should be attempted in the following 15 min with the opposite method (ET after ST or ST after ET) (= crossover treatment). If no haemostasis is achieved after a total time of approximately 30 min, alternative haemostasis methods such as topical haemostatic spray/powder, over-the-scope clip, angiographic coiling, or surgery can be used (= rescue treatment).

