### Sample size {14}

The study hypothesis is that experimental therapy is superior to standard therapy in terms of clinical success, defined as successful haemostasis and no (signs of) rebleeding within 30 days. In one study, the rates of successful haemostasis and rebleeding in the experimental group were 92.3% and 0%, respectively [9]. However, this nonrandomized trial also included nonactive nonvariceal bleeding. Therefore, the rate of successful haemostasis could be lower and the rate of rebleeding higher when only active nonvariceal bleeding is present. Therefore, a success rate of 90% for primary haemostasis and a rebleeding rate of 5% were assumed, giving a combined clinical success rate of 85.5%. In a recently published study comparing the Over-the-Scope Clip (OTSC) with the haemoclip in high-risk patients with acute nonvariceal upper gastrointestinal bleeding, the rates of successful haemostasis and rebleeding in the standard of care arm (haemoclip only) were 73.1% and 15.4%, respectively [12]. However, this randomized trial also included nonactive, nonvariceal bleeding. Therefore, the rate of successful haemostasis could be lower and the rate of rebleeding higher if only active nonvariceal bleeding is present. Therefore, a success rate of 72% for primary haemostasis and a rebleeding rate of 16% were assumed, resulting in a combined clinical success rate of 60.1%. Power analysis of the combined primary endpoint revealed that 45 patients per treatment arm are required to demonstrate an absolute difference of 25.4 percentage points (85.5–60.1%) with a power of 80% and a significance level of 0.05. Here, a simulation-based line calculation assuming the above absolute differences was performed using the SimEngine package version 1.1.0, implemented in R version 3.3.0. Overall, a dropout rate of a maximum of 10% is assumed, as the follow-up period is only 30 days. A decision on the recruitment of follow-up patients will be made when 90 patients have been included as planned and the follow-up observations are available.

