### Adverse event reporting and harms {22}

Adverse events (AEs) will be documented at the start of oral endoscope insertion and will end 30 days after the first haemostatic procedure. The type and number of adverse events are secondary outcome variables as defined above. Subsequent adverse events may no longer be directly related to details of the study or procedure. Overall, adverse events attributable to ST or ET are expected to be rare [3, 9]. An adverse event is defined as a serious adverse event (SAE) if it is fatal, life-threatening, or results in permanent or severe disability or incapacity. If an adverse event is classified as serious, it will be documented on a separate SAE form in addition to the AE documentation in the CRF. Patients will be asked at the 30-day query if any adverse or serious adverse events occurred. Adverse events will be documented in the CRF with the following parameters: date and time of occurrence and cessation, association with trial therapy, and outcome of the adverse event. Conditions that existed prior to the administration of the investigational product will be documented not as adverse events but as concomitant conditions. Any new disease or any disease that increases in severity during the trial shall be documented as an adverse event. Each adverse event shall be assessed by the investigator as to whether a relationship to the intervention can be suspected. The nature and pattern of the reaction, the temporal relationship with the intervention, the clinical condition of the patient, concomitant medication, and other relevant clinical parameters should be considered. If the event occurs due to lack of efficacy or due to the underlying disease, it shall be considered independent.

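### The only stated principle, intention-to-treat by arm, dilutes the forceps-versus-clip harm contrast because failures cross over to the other device; a descriptive by-device safety table should be added

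*Protocol article*

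**What the plan says.** - **Aim.** Under Objectives {7}: "The efficacy and safety of bipolar haemostatic forceps should be investigated", in primary treatment and against haemoclip with or without epinephrine injection.
- **Analysis principle.** The statistical methods section {20a}/{20b}, whose heading covers primary and secondary outcomes, states "An intention-to-treat analysis will be performed". For continuous variables, "differences between treatment arms will be analysed using linear regression"; binary and categorical outcomes go to logistic regression. No other analysis set is named.
- **Crossover.** Under {11b}, if the allocated method has not stopped the bleeding, "it should be attempted in the following 15 min with the opposite method (ET after ST or ST after ET". Rescue methods follow only after about 30 minutes.
- **Safety outcome.** Under Outcomes {12}, therapy-associated adverse events over 30 days are a secondary outcome, measured by description and count. The reason given is the safety of the methods, not of the randomised strategy. Crossovers are themselves counted as a secondary outcome.
- **Adverse event record.** Under {22}, each event is recorded with "date and time of occurrence and cessation, association with trial therapy, and outcome of the adverse event". The causality grades that follow refer to the intervention or test therapy in the singular.
- **Planning rates.** Under Sample size {14}, for ET "a success rate of 90% for primary haemostasis and a rebleeding rate of 5% were assumed"; for ST "a success rate of 72% for primary haemostasis and a rebleeding rate of 16% were assumed".

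**The concern.** The stated rule compares randomised arms, while the stated purpose of the adverse event outcome is to describe the methods. The two coincide only if each patient receives one device. Here exposure to both is built into the design and is unequal, because ST is expected to fail more often than ET. A forceps complication during crossover in an ST patient counts in the ST column of a by-arm table, and a clip complication during crossover counts in the ET column. The first displacement is expected to be the larger, so the forceps-minus-clip contrast shifts in favour of the forceps under most plausible risks.

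This matters because the Discussion looks towards first-line use of the forceps. A by-arm table alone would also leave about a fifth of the forceps-exposed patients out of any statement of the device's complication rate.

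**Working it through.** **Inputs from Sample size {14}.** 45 patients per arm; primary haemostasis 72% (ST) and 90% (ET). The 45 is reproducible: the unpooled normal formula for 85.5% against 60.1%, two-sided 0.05 and 80% power, gives 44.3, rounded up to 45, and exact enumeration gives 80.0% power for the chi-square test.

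**Inputs not in the article.** Complication risks per device are described only as rare. I write pF for forceps and pC for clip with or without injection, and take 1% to 10% and 0% to 5% as assumed ranges.

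**Step 1: implied crossover.**
- ST to forceps: 1 - 0.72 = 0.28; 0.28 x 45 = 12.6 patients (95% binomial range 7 to 19).
- ET to clip: 1 - 0.90 = 0.10; 0.10 x 45 = 4.5 patients.

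**Step 2: exposure by device.**
- Forceps: 45 + 12.6 = 57.6, of whom 12.6/57.6 = 21.9% are in ST.
- Clip: 45 + 4.5 = 49.5, of whom 4.5/49.5 = 9.1% are in ET.

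**Step 3: what a by-arm table shows.** Assume the two device risks act independently and are the same in first-line and crossover use.
- ET rate = 1 - (1 - pF)(1 - 0.10pC), about pF + 0.10pC.
- ST rate = 1 - (1 - pC)(1 - 0.28pF), about pC + 0.28pF.
- Difference: about 0.72pF - 0.90pC.
- Shift from the device contrast: (pF - pC) - (0.72pF - 0.90pC) = 0.28pF - 0.10pC. This is positive, and so works against seeing forceps harm, unless pC exceeds 2.8 times pF.

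**Step 4: examples** (risks assumed; arm rates from the full formulas).

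| pF | pC | Device difference (points) | ET rate | ST rate | Arm difference (points) |
|---|---|---|---|---|---|
| 5% | 0% | 5.0 | 5.00% | 1.40% | 3.6 |
| 5% | 2% | 3.0 | 5.19% | 3.37% | 1.8 |
| 5% | 5% | 0.0 | 5.48% | 6.33% | -0.85 |
| 10% | 2% | 8.0 | 10.18% | 4.74% | 5.4 |

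In no row is the ET rate below pF.

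**Step 5: events involved.** Expected forceps events in ST are 12.6 x pF: 0.13 at 1%, 0.63 at 5% and 1.26 at 10%.

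**Step 6: precision.** With no forceps event seen, the upper limit of the exact two-sided 95% interval is 1 - 0.025^(1/45) = 7.9% on the 45 ET patients and 1 - 0.025^(1/58) = 6.2% on about 58 exposed patients.

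**The case against.** Three stronger readings are tempting, and the article does not support them.

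- **That the forceps' risk is understated.** This is true of the contrast with clips, not of the rate in the ET arm, which is about pF + 0.10pC. Leaving out the ST crossovers costs precision but does not lower the estimate; with no events, the bound on 45 patients is the more cautious one.
- **That safety will be compared only by randomised arm.** The intention-to-treat sentence is general. It names no other set, but it does not exclude an as-received table, and an analysis plan that is not shown may define one.
- **That the device behind an event is not recorded.** The case report form and the separate form for serious events are not shown. The article does provide for event times, a description, a causality judgement and a count of crossovers, which will often identify the device. It does not say how causality is assigned when both were used. Timing alone may not settle a delayed perforation, which the article itself gives as an example of a probable event.

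Two further objections carry weight. The by-arm comparison answers a legitimate question: harm from starting with clips includes harm from what follows when clips fail. And the number of displaced events is small. Both are reasons to keep the by-arm table; neither removes the mismatch with the stated purpose of describing the methods. With counts this low, the column in which a single perforation appears could change the safety message.

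**Conclusion.** The point holds as a request for an added analysis. The one stated principle does not by itself answer the stated safety question, because planned crossover exposes about 28% of ST and 10% of ET patients to both devices. The between-arm harm contrast is then about 0.72pF - 0.90pC rather than pF - pC: 1.8 points instead of 3.0 at assumed risks of 5% and 2%, and slightly in favour of the forceps (-0.85 points) when both risks are 5%.

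This rests on the article's planning rates, on every primary failure crossing over, on device risks that are independent and unchanged in crossover use, and on complication risks the article does not give. The 28% and 10% are implied by those rates, not stated as crossover rates. The primary efficacy analysis is unaffected. Confidence is medium, since the analysis plan and the forms are not shown.

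**What to change.** 1. Keep the by-arm safety comparison. Add a sentence to the statistical methods section saying that adverse events will also be tabulated, descriptively, by treatment actually received: forceps only, clip with or without injection only, or both, with rescue treatment noted.
2. Give each device's complication rate over all patients exposed to it, with an exact confidence interval.
3. If the case report form does not already do so, state for which device causality is judged when both were used, with a separate entry for each device and for any rescue treatment.

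The cost is one sentence, one table and, at most, one split field on the form; crossover is already recorded. The downside is that the by-device table is not a randomised comparison. The group that received both devices consists of patients in whom the first method failed, so the table must be labelled descriptive and not used for a test between devices.

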**Fig. 2 Fig2:**
[figure not shown]
Settings of the HemoStat WideCup bipolar electric haemostatic forceps for different generators

Both experimental therapy (ET) and standard therapy (ST) are used primarily with the aim of stopping bleeding within a period of 15 min after locating the source of bleeding.

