### Methods in analysis to handle protocol nonadherence and any statistical methods to handle missing data {20c}

N/A, as protocol nonadherence and missing data are not expected as the intervention is performed by the endoscopist and the follow-up period is short (30 days).

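### Linear regression does not fit time to initial haemostasis, because about 17 of 90 patients are expected to have no time within 15 minutes, and its clock starts at a different point from the primary endpoint's

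*Protocol article*

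**What the plan says.** **Outcome.** The last item under Secondary and other outcomes is the time to complete initial haemostasis, in minutes, over a period of 15 minutes counted from the start of haemostasis.

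**Model.** Statistical methods {20a}/{20b} opens with "An intention-to-treat analysis will be performed" and continues: "For continuous variables, differences between treatment arms will be analysed using linear regression", with possible adjustment for confounders. Time to haemostasis is neither named nor exempted.

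**Failures.** Criteria for discontinuing or modifying allocated interventions {11b} says: "If no haemostasis is achieved, it should be attempted in the following 15 min with the opposite method". For the experimental arm, Sample size {14} says "a success rate of 90% for primary haemostasis and a rebleeding rate of 5% were assumed"; for the standard arm, "a success rate of 72% for primary haemostasis and a rebleeding rate of 16% were assumed".

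**Missing data.** The section on nonadherence and missing data {20c} reads "N/A, as protocol nonadherence and missing data are not expected". Its reasons are that the endoscopist delivers the treatment and that follow-up is short.

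**Clock for success.** The text after Figure 2 says that both treatments are used "with the aim of stopping bleeding within a period of 15 min after locating the source of bleeding". Primary outcome measure also counts its 15 minutes from localisation.

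**The concern.** A patient who is still bleeding at 15 minutes moves to the other method and so has no haemostasis time under the assigned one. The protocol gives such patients neither a value nor a censoring rule. If the regression is run on the times that are recorded, it compares successes only. That subset is defined by a result that arises after randomisation, and it is expected to be smaller in one arm than in the other. An arm that stops only the easy bleeds can then look fast.

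Separately, the two outcomes measure their 15 minutes from different points. If time passes between localisation and the start of treatment, one patient's record can show haemostasis in under 15 minutes and a primary failure together. At stake are the interpretation of the speed comparison and a clear reading of the window that defines primary success.

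**Working it through.** **1. The protocol's planning figures.** Two-sided alpha of 0.05 is assumed, since sidedness is not stated. The unpooled formula gives n = (1.96 + 0.8416)² × (0.855 × 0.145 + 0.601 × 0.399) / 0.254² = 7.849 × 0.3638 / 0.0645 = 44.3, rounded up to the stated 45 per arm. The pooled formula gives 47. (0.72 × 0.84 is 60.5%, not the printed 60.1%; this does not bear on the present point.)

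**2. Patients without a time.** This uses only the protocol's rates:
- ST: 45 × (1 − 0.72) = 12.6
- ET: 45 × (1 − 0.90) = 4.5
- Total: 17.1 of 90, or 19%
- Times recorded: 45 × 0.72 = 32.4 (ST) and 45 × 0.90 = 40.5 (ET)

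The rates refer to the clock from localisation. The arithmetic below lets the two clocks coincide.

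**3. Effect on the comparison.** The documents give no distribution of times, so three were assumed, each with 72% and 90% controlled by 15 minutes. The mean among successes is set against the mean over all patients with failures held at 15 minutes, which is the restricted mean. Differences are ST minus ET, so a positive value favours ET.

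*(a) Exponential times.* With S the share not controlled at 15 minutes, the rate is −ln(S)/15.
- ST: S = 0.28, 1/rate = 11.78. Among successes: 11.78 − 15 × 0.28/0.72 = 5.95. Restricted mean: 0.72 × 11.78 = 8.48.
- ET: S = 0.10, 1/rate = 6.51. Among successes: 6.51 − 15 × 0.10/0.90 = 4.85. Restricted mean: 0.90 × 6.51 = 5.86.
- Difference: 1.1 min among successes, 2.6 min over all patients.

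*(b) Same success times in both arms, uniform on 1 to 14 min (mean 7.5).*
- Among successes: 7.5 − 7.5 = 0.
- All patients: (0.72 × 7.5 + 0.28 × 15) − (0.90 × 7.5 + 0.10 × 15) = 9.60 − 8.25 = 1.35 min.

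*(c) ET's extra 18% of successes come late.* In both arms 72% succeed at 1 to 10 min (mean 5.5). ET adds 18% at 10 to 15 min (mean 12.5).
- Among successes: 5.5 − (0.72 × 5.5 + 0.18 × 12.5)/0.90 = 5.5 − 6.9 = −1.4 min, which favours ST.
- All patients: (3.96 + 4.20) − (3.96 + 2.25 + 1.50) = 8.16 − 7.71 = 0.45 min, which favours ET.

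Simulation at 45 per arm (5,000 trials per scenario) gave these two-sided rejection rates. The t-test is the unadjusted form of the planned regression.

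| Scenario | t-test, successes only | t-test, failures at 15 min | Rank test, failures at 15 min |
|---|---|---|---|
| (a) | 22% | 67% | 64% |
| (b) | 5% | 29% | 31% |
| (c) | 43% | 7% | 7% |

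**4. The two clocks.** Let d be the time from localisation to the start of haemostasis, and t the recorded time from that start. Primary success requires d + t ≤ 15; the time outcome admits any t ≤ 15. Whenever d > 0, a patient with 15 − d < t ≤ 15 has a valid time and is a primary failure. The protocol gives no value for d. Assignment of interventions {16} places randomisation during endoscopy, once a patient is known to be eligible, so d need not be zero.

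**The case against.** **The protocol does not say that failures are dropped.** This is correct. The methods section does not name this outcome, promises intention to treat, and could be followed with failures entered at 15 minutes. Linear regression on those values would estimate the restricted mean difference itself. An analysis plan that is not shown may say so. A reader might infer that exclusion of failures is planned; the text does not support that. What stands is narrower: the stated rule, read as written, needs a number of minutes that about 19% of patients will not have, and the one section that would cover the gap is marked not applicable.

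**The size rests on assumptions.** A reader of scenario (a) might conclude that the planned analysis shows less than half of the true difference. That ratio belongs to the exponential assumption, and it compares two different quantities: a mean among successes and a restricted mean over all patients. The reversal in (c) was built by placing ET's extra successes late. The scenarios show what can happen, not what will.

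**The clock conflict may touch few patients.** Under {11b} the method should change at 15 minutes. Read with the clock that starts at localisation, a discordant record needs treatment to run past the switch, or a crossover success to be entered as initial haemostasis. So the two outcomes may disagree; it does not follow that they will. The difference in wording remains.

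**Other outcomes.** A reader might extend the point to transfused units, reinterventions and lengths of stay. The documents do not support that. The methods section does not say which model counts receive, and describing skewed data by medians while comparing means by regression is not a contradiction.

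**Low priority.** The outcome is the last in its list and is absent from the objectives in section {7}. This limits the weight of the point but does not answer it.

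**Conclusion.** The point holds in limited form. The linear regression rule does not fit time to initial haemostasis: by the protocol's own rates, about 12.6 of 45 ST and 4.5 of 45 ET patients will have no time under the assigned method within 15 minutes, and the expectation of no missing data does not fit those rates. These counts need no outside assumption beyond treating the two clocks as one. Regression on recorded times can shrink the difference (2.6 to 1.1 min), remove it (1.35 to 0 min) or reverse it (0.45 min for ET to 1.4 min for ST), depending on the assumed distribution of times.

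The start of the 15 minutes is stated inconsistently, so a patient may count as a timed success and as a primary failure. How often cannot be told from the documents.

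The regression issue leaves the primary analysis untouched. The clock issue bears on the primary endpoint only in that the window should be read in one way by all sites.

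**What to change.** 1. Reconcile the start of the 15 minutes in the text after Figure 2, in Primary outcome measure and in Secondary and other outcomes, so that one recorded clock serves both outcomes. Because the same window governs the switch of method, the choice of start belongs to the investigators.
2. State that time to initial haemostasis is analysed in all randomised patients by assigned arm, with patients not controlled under the assigned method censored at 15 minutes. Report the difference in restricted mean time to 15 minutes with its confidence interval, and a log-rank test stratified by centre. A rank test with failures ranked worst is an acceptable alternative.
3. Treat a patient who is switched before 15 minutes as not controlled through 15 minutes, rather than censoring at the switch, because the switch itself signals failure.
4. Replace the not-applicable entry in {20c}, for this outcome, with a reference to that rule.

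The cost is a few sentences of analysis-plan wording and one time-stamp definition in the case report form. The form is not shown, so whether it already records both localisation and start of treatment should be checked first. No change to sample size, and no new procedure, is needed.

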**Discussion:**

The hypothesis of the study is that bipolar haemostatic forceps are superior to ST in terms of successful primary haemostasis and the absence of recurrent bleeding within 30 days (combined endpoint). The 1:1 randomization is also ethically justifiable for this study, as both procedures are approved for the intervention in question. To further increase the safety of the patients in the study, crossover treatment and rescue treatment are planned. The prospective design seems feasible in a reasonable time frame (recruitment period of 12 months), as nonvariceal upper gastrointestinal bleeding is common. Anticoagulants and/or antiplatelet drugs could be an important confounding factor in the statistical analysis that needs to be taken into account and calculated if necessary. In conclusion, this randomized, prospective, multicentre study could make an important contribution to answering the question of whether bipolar haemostatic forceps could be the first-line therapy in the endoscopic treatment of stage Forrest I a + b NVUGIB.

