### Trial design {8}

The trial design is as follows: prospective, multicentre superiority trial with 1:1 randomization of standard therapy versus experimental therapy.

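### The protocol does not fix one test of the treatment effect on the combined primary endpoint, and its confounder list includes the randomised therapy itself

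*Protocol article*

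**What the plan says.** The protocol article describes the analysis of the primary endpoint only in its statistical methods section, whose heading covers both {20a} and {20b}. It states four things that matter here.

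- Analysis is by intention to treat, and binary outcomes get logistic regression. Correction for confounders is only a possibility, and no criterion says when it applies.
- The confounders are given as examples: centre, age, antithrombotic drugs, Forrest class, ulcer size and location, *H. pylori* status and others. The list ends with "prior endoscopic treatment, and standard or bipolar haemostatic forceps therapy".
- Variables with p below 0.05 "in the univariate model will be entered into a multivariate stepwise logistic regression model (forwards selection, likelihood ratio". The stated aim is to assess the independent predictive effect of the variables of interest.
- On antithrombotic drugs, the Discussion part of the abstract says that this factor "needs to be taken into account and calculated if necessary". The main Discussion says much the same.

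The sample size section powers a single comparison: "45 patients per treatment arm are required to demonstrate an absolute difference of 25.4 percentage points (85.5–60.1" per cent), "with a power of 80% and a significance level of 0.05". The design is "1:1 randomization of standard therapy versus experimental therapy". The allocation section stratifies randomisation by centre in blocks of 4, yet centre appears in the analysis only as a possible covariate.

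**The concern.** A superiority claim from 90 patients needs one test that is identifiable before the data are seen. This text leaves several open: unadjusted, adjusted for some or all of an open list, or adjusted for whatever survives selection on p values. The Bonferroni sentence in the same section concerns subanalyses and does not cover this choice.

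Randomised therapy cannot be a confounder of its own comparison. Listing it makes it one more candidate for the screen. Read literally, treatment then enters the multivariable model only if it is already significant, so a non-significant trial has no adjusted estimate or confidence interval to report. Two things are at stake: whether the 5% level is kept, and whether there is a treatment estimate at all.

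**Working it through.** **Inputs from the sample size section.** Success is 85.5% with forceps (0.90 × 0.95 = 0.855) and 60.1% with standard therapy, with 45 patients per arm, α 0.05 and power 80%. Sidedness is not stated; I assume two-sided. (0.72 × 0.84 is 0.6048 rather than 0.601. That is a separate matter, and I use the stated 60.1%.)

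**Which test fits the plan's own figure?** For two proportions, n per arm = [1.96·√(2p̄q̄) + 0.8416·√(p₁q₁ + p₂q₂)]² / δ².

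- p̄ = (0.855 + 0.601)/2 = 0.728, so √(2 × 0.728 × 0.272) = 0.6293.
- √(0.855 × 0.145 + 0.601 × 0.399) = √0.3638 = 0.6031.
- n = (1.2335 + 0.5076)² / 0.254² = 3.031/0.0645 = 47.0.

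Exact enumeration at 45 per arm gives 80.05% power for an unadjusted Pearson or likelihood-ratio test. The planned size therefore agrees with an unadjusted comparison, but no section names that test as primary.

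**Information available for adjustment.** Expected failures are 45 × 0.399 + 45 × 0.145 = 17.96 + 6.53 = 24.5. If every listed variable were entered, the coefficients would be centre 4, age 1, anticoagulant 1, antiplatelet 1, Forrest 1, size 1, location 2, *H. pylori* 1, prior treatment 1 and arm 1, which is 14. That is 24.5/14 = 1.7 failures per coefficient, or roughly 2. The count assumes exactly five centres (the protocol says at least five), three locations and separate drug terms.

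**Type I error by simulation.** The setting was 90 patients, 5 centres, blocks of 4, 73% success in both arms and likelihood-ratio tests at 0.05, with 18,000 null trials per scenario (Monte Carlo standard error 0.16 points). Covariate effects are assumptions: either none, or moderate. Moderate means log-odds shifts of -0.3 and -0.6 per SD for two continuous variables, and -0.6, -1.0 and -0.4 for three binary variables with prevalence 50%, 30% and 50%.

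| Rule | No effects | Moderate effects |
|---|---|---|
| Unadjusted | 5.2% | 5.4% |
| Screen and forward selection, arm as a candidate | 4.9% | 3.9% |
| Covariates chosen stepwise, arm then added | 5.3% | 5.6% |
| All listed covariates plus arm | 7.2% | 7.8% |
| Either unadjusted or stepwise-adjusted significant | 5.7% | 7.1% |
| Any of unadjusted, stepwise-adjusted or full significant | 8.2% | 9.9% |
| Fixed: arm, Forrest class, antithrombotic use | 5.5% | 5.8% |
| Fixed: arm and centre | 5.8% | 6.0% |

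**Power at 85.5% against 60.1%** (2,000 trials per scenario; no effects, then moderate effects).

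- Unadjusted: 79.1% and 77.6%.
- Screen and selection with arm as a candidate: 78.1% and 74.7%, a loss of about 1 and 3 points.
- Arm is left out of the final model in 100 - 78.1 = 21.9% and 100 - 74.7 = 25.3% of trials, although the planned effect is present.
- Fixed model with Forrest class and antithrombotic use: about 79% in both.

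**The case against.** The best defence is that the stepwise sentence is not about the treatment effect. It stands apart from the sentences on arm differences, follows the text on subanalyses, has a predictive aim, and sits under a heading that also covers additional analyses. On that reading therapy is an ordinary candidate predictor, and the arm comparison is a logistic regression that fits the unadjusted power calculation. A final covariate set is also commonly left to a statistical analysis plan, which is not shown here. The remark on antithrombotic drugs is discussion text, and it does not say when the decision would be taken.

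Much of this stands. The predictor reading is possible, and a reader who infers that adjustment of the treatment effect is definitely handed to the stepwise procedure goes beyond the text. What remains is that the section does not label the step exploratory, puts therapy in the list of things to correct for, and leaves correction of the arm comparison optional even if the stepwise sentence is set aside. These are rules stated badly, not details left out.

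A reader might also infer that the plan's error rate is in fact inflated, or about doubled, and that the odds ratio will be exaggerated. The documents do not support this. The stepwise rule applied mechanically is at or below 5%. Rates of 8-10% need selective reporting across models that include a full model, which the protocol permits but does not prescribe. Marked overfitting of the odds ratio would likewise require that full model.

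**Conclusion.** The point holds as a failure to fix the primary test. The endpoint, the intention-to-treat principle and the model family are stated; the covariates, the status of the stepwise step and the place of arm in the model are not settled. Depending on which permitted route is taken, simulated type I error runs from about 4% to about 10%. It is about 4-5% if arm must survive selection, about 6-7% if unadjusted and stepwise-adjusted results can be chosen between, and 8-10% if the full model is also available.

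The size depends on assumed covariate effects, five centres and, for the upper figures, a choice made after seeing the data. With no prognostic effects at all, the three-way choice still gives 8.2%, so that part does not hang on the assumed effects. The exact rate cannot be derived from the document. Rates slightly above 5% for the unadjusted and fixed models reflect likelihood-ratio tests in a small sample and are not evidence against pre-specification. The consequence that needs no simulation is that, if the selection rule governs the arm comparison, a treatment that is not selected has no adjusted estimate.

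**What to change.** In {20a}:

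1. Name one primary analysis: logistic regression of the combined endpoint with arm always in the model, adjusted only for a short set fixed before database lock. That set is centre as the stratification factor (small centres pooled if needed), plus at most Forrest Ia/Ib and baseline antithrombotic use. Report the unadjusted comparison as supportive.
2. Delete the randomised therapy from the list of confounders.
3. Restrict univariate screening and stepwise selection to an analysis labelled as exploratory prediction, and state that no treatment claim rests on it.

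With five unpooled centres this model has 1 + 4 + 1 + 1 = 7 coefficients, or 24.5/7 = 3.5 expected failures each. This is why the set should not grow and why pooling matters. The full combination was not simulated (its parts gave 5.5-6.0% error), so its error rate should be checked before it is fixed.

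The cost is a few sentences, with no extra patients or data. The downside is that the freedom to adjust later for a chance imbalance is lost.
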